# Preoperative CT versus intraoperative hybrid DynaCT imaging for localization of small pulmonary nodules: a randomized controlled trial

**DOI:** 10.1186/s13063-019-3532-z

**Published:** 2019-07-04

**Keywords:** Hybrid operating room, Slitary pulmonary nodules, Localization, ARTIS zeego

## Abstract

**Background:**

Localization of small and/or deep pulmonary nodules before thoracoscopic exploration is paramount to minimize the likelihood of unplanned conversion to thoracotomy. As far as the percutaneous approach is concerned, the most common workflow consists of preoperative computed tomography (POCT) imaging-guided tumor marking (performed in an interventional CT suite) followed by their removal in an operating room (OR). However, the advent of hybrid ORs has allowed intraoperative computed tomography (IOCT)-guided lesion localization. This single center, open-label, randomized, controlled clinical trial aims to compare the efficacy and safety of IOCT versus POCT.

**Methods/design:**

The study sample will consist of patients presenting with small and/or deep pulmonary nodules who will be randomly allocated to either POCT or IOCT. The time required to complete lesion localization will be the primary efficacy outcome. The following parameters will serve as secondary endpoints: rate of successful targeting during localization and in the operating field, time at risk, operating time, length of time under anesthesia, global OR utilization time, complication (pneumothorax and hemorrhage) rates, and radiation exposure.

**Discussion:**

Owing to the increased availability of HORs, our data will be crucial to clarify the feasibility and safety of IOCT versus the traditional POCT approach.

**Trial registration:**

ClinicalTrials.gov, NCT03395964. Registered on October 8, 2018.

**Electronic supplementary material:**

The online version of this article (10.1186/s13063-019-3532-z) contains supplementary material, which is available to authorized users.

## Background

With the implementation of lung cancer screening based on low-dose computed tomography (CT), the number of patients diagnosed with small and/or deeply located pulmonary nodules has markedly increased. Lesions detected during screening should be carefully evaluated and eventually removed (when their malignant nature is highly suspected) [1]. However, their excision through video-assisted thoracoscopic surgery (VATS) may be challenging, particularly when such nodules are small (< 10–15 mm in size) and/or deeply located (> 5–10 mm from the pleural surface) in the lung parenchyma [2, 3]. Efficient and safe tumor marking before embarking on VATS is paramount to avoid an unplanned conversion to thoracotomy [4]. To this aim, several approaches have been proposed, including percutaneous CT-guided [5–8], bronchoscopy-guided (grounded in segmental anatomy and virtual imaging) [9, 10], and electromagnetic navigation bronchoscopy (ENB)-guided [11–13] methods. The results of a randomized study have previously shown that preoperative lesion localization is superior to no localization in terms of increased number of successful VATS wedge resections, reduced surgical time, and less frequent use of staples [3]. Moreover, total costs did not increase appreciably.

As far as the percutaneous approach is concerned, the most common workflow consists of preoperative computed tomography (POCT) imaging-guided tumor marking (performed in an interventional CT suite) followed by their removal in an operating room (OR) [5, 8]. However, this two-step methodology requires careful planning in order to avoid complications (e.g., pneumothorax, hemothorax, wire dislodgement, dye diffusion), the incidence of which increases in parallel with the time elapsed from localization to surgery.

The recent advent of hybrid ORs is triggering a paradigm shift in the treatment of pulmonary nodules, paving the way to intraoperative CT (IOCT)-guided VATS. Although numerous studies have already shown that IOCT is clinically feasible [14–16], the question as to whether this approach is superior to traditional POCT remains open [17]. To address this issue, well-designed prospective randomized studies are eagerly awaited [18]. Here, we describe the protocol of a single-center prospective study that aims to provide a direct head-to-head comparison of IOCT versus POCT for localizing pulmonary nodules. The two techniques will be investigated in relation to efficacy, accuracy, complications, and radiation exposure.

## Methods/design

### Study design

Figure 1 depicts the flow of this investigator-initiated, investigator-driven study, which was designed as a single-center, open-label, randomized controlled trial. Patients diagnosed with pulmonary nodules and scheduled to undergo tumor localization before VATS will be randomized (1:1 ratio) to either IOCT or POCT.

**Fig. 1 Fig1:**
[figure not shown]
Flowchart of the study

### Study patients

Subjects aged at least 18 years will be considered eligible for the study if they have a lung tumor requiring localization before VATS. Localization will be deemed necessary when one of the following criteria is met: 1) presence of solid pulmonary nodules of less than 10 mm in size and/or with a distance from the visceral pleura to the edge of nodule of at least 10 mm; or 2) evidence of subpleural cavitary lesions/ground glass nodules (GGNs), independent of their size and/or depth.

Exclusion criteria will be as follows: 1) presence of more than one nodule requiring localization; 2) inability to provide written informed consent; and 3) unwillingness to adhere to the proposed follow-up protocol.

### Screening for inclusion

Potentially eligible patients will be approached about potential inclusion either during the prehospitalization visit or while being hospitalized (before scheduled surgery). Complete information about the study objectives will be provided to all candidates.

### Randomization

Patients will be randomized to either IOCT or POCT (1:1 ratio) using a computerized randomization tool. We will implement a permuted-block randomization scheme with varying block sizes, while maintaining both allocation and block sizes concealed to the study investigators. Owing to the obvious procedural differences between IOCT and POCT, blinding of surgeons and patients cannot be achieved. In order to ensure an objective evaluation of the endpoints, all of the study outcomes will be investigated by an independent assessor (blinded to the allocation of patients to either POCT or IOCT) through a careful review of clinical records. After randomization, patients will be excluded when tumor regression or progression will be evident on prelocalization images (ultimately abrogating the need of localization). Patients will be allowed to exit from the study at any time.

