### Primary outcome measure

The time required for lesion localization will be the primary outcome measure. In the POCT group, it will be defined as the time elapsed from the beginning of preprocedural CT imaging to the end of postprocedural CT scan. In the IOCT group, it will be calculated from the docking of the C-arm to the end of the procedure (i.e., retraction of the C-arm from the table to the park position).

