### Secondary endpoints

The following secondary endpoints will be examined: 1) successful targeting rates during localization (defined as the number of successful targeting procedures divided by the number of all localization procedures); 2) successful targeting rates in the operating field (defined as the number of successful targeting procedures minus the number of wire dislodgements or dye fading/spillage occurring in the operation field divided by the number of all localization procedures); 3) time at risk (defined as the time elapsed between the completion of localization and skin incision); 4) other time parameters (including operating time, length of time under anesthesia, global operation room utilization time, and length of hospital stay); 5) rate of conversion to thoracotomy; and 6) complication rates. The occurrence of complications (including pneumothorax and lung hemorrhage) will be recorded after the initial follow-up CT scan following localization. According to the 2010 British Thoracic Society guidelines, large or small pneumothorax will be defined by a distance between the lung margin and chest wall greater or less than 2 cm, respectively [21]. As far as radiation doses are concerned, we will quantify the radiation dose delivered to patients by determining the effective dose (ED). During POCT procedures, the radiation dose delivered by MDCT will be determined using the dose length product (DLP) and expressed as mGy/cm. The radiation dose will be converted to the ED using a suitable conversion factor (0.014, mSvGy^− 1^ cm^− 1^) [22]. During IOCT procedures, the radiation doses delivered by both CBCT and fluoroscopy will be determined using the dose area product (DAP) and expressed as mGy/cm^2^. Two appropriate conversion factors (0.146 and 0.12 mSvGy^− 1^ cm^− 2^) will be used to calculate the ED for CBCT and fluoroscopy, respectively [23, 24]. Four sets of thermoluminescent dosimeters (TLDs; UD-802A; Panasonic, Osaka, Japan) will be also placed around the patient’s chest wall (in proximity to the lesion of interest). The radiation dose absorbed by each TLD will be measured using a TLD reader (UD-716AGL TLD reader; Panasonic, Tokyo, Japan) and mean values will be used for analysis.

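### The claim that all outcomes are assessed blind to arm cannot hold, as described, for the primary localization time or for radiation dose

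*Protocol article*

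**What the plan says.** The protocol article describes an open-label trial. Its Randomization section accepts that "blinding of surgeons and patients cannot be achieved" and then offers a safeguard for objective endpoint evaluation: "all of the study outcomes will be investigated by an independent assessor (blinded to the allocation of patients to either POCT or IOCT"). The stated means is "through a careful review of clinical records".

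The section on the primary outcome measure says: "The time required for lesion localization will be the primary outcome measure". The definition depends on the arm:

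- POCT: "the time elapsed from the beginning of preprocedural CT imaging to the end of postprocedural CT scan".
- IOCT: "it will be calculated from the docking of the C-arm to the end of the procedure", which the article explains as the C-arm being withdrawn from the table and parked.

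The Secondary endpoints section also treats radiation dose by arm. For POCT, "the radiation dose delivered by MDCT will be determined using the dose length product (DLP"). For IOCT, "the radiation doses delivered by both CBCT and fluoroscopy will be determined using the dose area product (DAP"). Each route has its own conversion to effective dose.

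**The concern.** The blinding statement covers every outcome and names how the assessor will work. The outcome definitions do not allow that way of working for the primary endpoint: an assessor who takes localization time from the records has to decide which pair of events applies, and the events themselves identify the arm.

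This matters because surgeons and patients are unblinded, which leaves the assessor as the only blinding safeguard the article offers. If the sentence is carried into the trial report, readers will credit the primary result with a protection against detection bias that the described process does not give. It is not a gap that a condensed article may leave to a fuller document, because the article makes a positive claim and its own endpoint definitions conflict with it.

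**Working it through.** No arithmetic bears on this point: the article gives no figure that tests a blinding claim. The check is to take each group of outcomes and ask whether an assessor reading clinical records could determine it without learning the arm.

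1. **Localization time (primary).** In POCT the clock runs between two CT imaging events; in IOCT it runs between two C-arm positions. The two rules share no event. Applying the right rule requires the arm, and finding either pair of events in the record discloses it. Blinding fails as described.

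2. **Radiation dose.** In POCT the input is DLP, multiplied by one factor (0.014). In IOCT the input is DAP, with two factors (0.146 for cone-beam CT, 0.12 for fluoroscopy). The calculation cannot be set up without the arm. The Discussion also speaks of dosimeters for the IOCT arm. Blinding fails as described.

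3. **Other procedural times.** Time at risk runs from the end of localization to skin incision. Under POCT-guided localization the patient goes to a general ward in between; under IOCT-guided localization, marking and removal take place in one session after induction of anesthesia. The records needed for time at risk, anesthesia time and OR utilization therefore show the pathway.

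4. **Targeting success, pneumothorax and hemorrhage.** These are judged around localization and on the scan that follows it, which is from the CT scanner in POCT and cone-beam CT in IOCT. Microcoil and near-infrared dye are described only for IOCT. Records and images would normally reveal the modality. Blinding is doubtful, because no masking step is described.

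5. **Conversion to thoracotomy.** In IOCT, localization and resection share one operative session, so the operative record may itself disclose the arm. Whether this can be masked is uncertain.

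6. **Readmission, death and later postoperative complications.** These are collected up to 90 days after surgery and do not depend on arm-specific definitions. They could be assessed blind from extracts with localization site and modality removed.

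The claim is thus contradicted for groups 1 and 2, doubtful for groups 3 to 5, and achievable with masking for group 6.

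**The case against.** The best defence has three parts.

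First, a duration is a single number. Coordinators or nurses could extract it and pass an arm-free value to the assessor. The section on data collection and management shows that such staff exist and that case record forms are checked against sources. A reader might otherwise infer that blinding is impossible in every patient; that goes too far, because another workflow could preserve it in part. The workflow described, however, is the assessor's own review of clinical records. If someone else derives the time first, that person, who knows the arm, is the one who measures the primary outcome. The sentence would still need correcting.

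Second, the clock events are discrete physical events, and pneumothorax size has a 2 cm cut-off. This stands: an assessor has little discretion over the primary outcome. A reader might infer that the primary comparison is biased, but nothing in the documents shows that. One could assume a shift in SD units and compute an inflated false-positive rate at 24 patients per arm. The article gives no SD and no reason to expect any particular shift, so the result would describe only the assumption, and none is offered here.

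Third, the trial is openly declared open-label, so the correction mainly concerns accurate reporting. This also stands. It limits the severity but does not remove the contradiction.

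**Conclusion.** The point holds in a limited form. The statement that all outcomes are assessed blind is incompatible with the article's own definitions of the primary outcome and of radiation dose, and is unsupported for the other localization-related outcomes. The contradiction applies to the primary endpoint in both arms and so to every patient.

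The conclusion assumes that the assessor derives the outcomes from clinical records, as the Randomization section says, and that no masking takes place, since none is described. It does not extend to the reading that blinded assessment is absent from the trial altogether: readmission, death and later complications can be masked. Nor does it establish detection bias of any size. The consequence is a misstatement of how well the primary endpoint is protected. It should be corrected, but it does not invalidate the design.

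**What to change.** Withdraw the claim that all outcomes are assessed blind, and replace it with three statements:

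- **Unblinded, rule-based.** Localization time, the other procedural times and radiation dose are assessed with knowledge of the arm. Times are taken from contemporaneously recorded time stamps (scanner, C-arm, or OR and anesthesia records, as available) under an extraction rule fixed in advance and applied in both arms. The article does not say which of these sources exist, so the sponsor must confirm them.
- **Blinded.** Readmission, death and later postoperative complications are assessed from extracts with localization site and modality removed. Conversion to thoracotomy should be included only if the operative record can be masked in practice.
- **Open-label.** The remaining localization outcomes (targeting success, and pneumothorax and hemorrhage on the scan after localization) are reported as such.

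The cost is protocol wording and modest time for the existing coordinators to prepare extracts. Sample size, endpoints and the statistical test do not change. The downside is that the trial's stated blinding looks less favourable.

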### POCT-guided localization

All POCT-guided localization will be performed on a CT scanner (GE BrightSpeed; GE Healthcare, Milwaukee, WI, USA; Fig. 2a) by a single team of interventional radiologists according to a previously described workflow [8]. Before implementing the procedure, case images will be reviewed to determine the most suitable needle trajectory. Sterile wraps will be positioned around the patient’s chest, followed by injection of 1% lidocaine at the site of needle insertion in the chest. A scalpel will be subsequently used to create a small skin incision followed by the insertion through the chest wall of a 10.7-cm-long, 20-gauge cannula needle containing a double-thorn hookwire (length 20 cm; DuaLok®, Bard Peripheral Vascular Inc., Tempe, AZ, USA). Under intermittent CT guidance, the needle will be positioned at the edge of the nodule of interest. As soon as the needle tip is close to or reaches the lesion, the hookwire will be advanced through the cannula. PBV dye (0.5 mL, patent blue V 2.5%; Guerbet, Aulnay-sous-Bois, France) injected through a 22-gauge, 8.9-long spinal needle will be used to localize superficial lesions (Fig. 2b). The proper reciprocal positioning of the lesion and hookwire will be investigated through an immediate follow-up CT scan. Upon completion of localization, patients will be moved to a general ward before undergoing the scheduled resection.

**Fig. 2 Fig2:**
[figure not shown]
**a** Interventional radiology suite equipped with a 16-slice CT scanner (GE BrightSpeed; GE Healthcare, Milwaukee, WI, USA). **b** PBV dye injection following needle localization

### IOCT-guided localization

Patients in the IOCT group will undergo lesion localization in a hybrid OR equipped with C-arm cone-beam computed tomography (CBCT; ARTIS zeego; Siemens Healthcare GmbH, Erlangen, Germany) and a Magnus surgical table (Maquet Medical Systems, Wayne, NJ, USA) (Fig. 3a). The nodules will be localized and subsequently removed in a unique section by a single team of thoracic surgeons according to a previously described workflow [19]. After induction of general anesthesia, patients will be positioned in the lateral decubitus. A 6-s protocol (6 s DynaCT Body) will be used to acquire an initial scan for surgical planning (with the patient under end-inspiratory breathhold). We will model the needle entry path in the isotropic data set under the syngo Needle Guidance provided with the syngo X-Workplace (Siemens Healthcare GmbH). The needle trajectory will be initially identified by marking the entry and target points. A laser-target cross will be projected onto the patient’s surface to visualize the needle entry point and angulation. An 18-gauge marker needle will be deployed into the patient’s thorax during end-inspiratory breathhold under three-dimensional laser guidance and guided fluoroscopy (Fig. 3b). CBCT will be used to confirm an appropriate needle positioning, and the lesion will be subsequently localized using either a hookwire (DuaLok®; Bard Peripheral Vascular Inc.) or a microcoil (Cook Medical, Bloomington, IN, USA). Superficial lesions will be identified through the injection of either PBV (0.3–0.5 mL, patent blue V 2.5%; Guerbet, Villepinte, France) or near-infrared dye as previously described [20].The correct lesion localization will be confirmed through a post-procedural CBCT scan.

**Fig. 3 Fig3:**
[figure not shown]
**a** Hybrid operating room equipped with a cone-beam CT apparatus (ARTIS zeego; Siemens Healthcare GmbH, Erlangen, Germany) and a Magnus surgical table (Maquet Medical Systems, Wayne, NJ, USA). **b** The needle entry point and angulation were visualized by projecting a laser-targeting cross onto the patient’s surface

### Surgical treatment

Patients in both arms will undergo VATS wedge resection, with the resected specimen being submitted to frozen section examination. Cases with a confirmed diagnosis of primary lung cancer will undergo lobectomy. Patients unable to tolerate lobectomy because of an inadequate pulmonary function or with peripheral lung cancer of limited size (< 2 cm) and adequate resection margins (either > 2 cm or bigger than tumor size) will be treated with a sublobar resection (wedge resection or segmentectomy).

### Data collection and management

Each participant will be unequivocally identified through a personal code (accessible to the principal investigator and the study coordinators only) assigned at inclusion. Digital case record forms (CRF) compliant with good clinical practice standards will be used for data collection and managed by the study coordinators and/or research nurses. Paper records will be stored in secured cabinets located at the data coordinating centers, with access being granted to the principal investigator and other researchers (nurses and physicians). Request for consultation of raw data (upon completion of the study) should be directed to the principal investigation. In order to ensure that the primary and secondary study outcomes will be accurately reported, all CRFs will be thoroughly cross-checked with the original sources. Clinical data will be stored in an anonymized fashion in keeping with local privacy laws.

### Primary outcome measure

The time required for lesion localization will be the primary outcome measure. In the POCT group, it will be defined as the time elapsed from the beginning of preprocedural CT imaging to the end of postprocedural CT scan. In the IOCT group, it will be calculated from the docking of the C-arm to the end of the procedure (i.e., retraction of the C-arm from the table to the park position).

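### The primary outcome, localization time, starts and stops at non-equivalent events in the two arms, so part of any difference comes from the definition

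*Protocol article*

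**What the plan says.** Under Primary outcome measure, the protocol article states: "The time required for lesion localization will be the primary outcome measure". It then gives each arm its own clock.

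- POCT: "the time elapsed from the beginning of preprocedural CT imaging to the end of postprocedural CT scan".
- IOCT: "In the IOCT group, it will be calculated from the docking of the C-arm to the end of the procedure", where the end is explained as "retraction of the C-arm from the table to the park position".

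The section IOCT-guided localization shows that this arm also has a first and a last scan. A DynaCT acquisition "will be used to acquire an initial scan for surgical planning", and the correct localization "will be confirmed through a post-procedural CBCT scan".

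The section Sample size calculation sizes the trial on a two-sample t-test of equal localization time, with 24 patients per arm (27 after dropout). The Discussion again names this time as the primary endpoint. No section explains why the two windows differ or adjusts for it.

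**The concern.** The POCT clock is bounded by imaging events and the IOCT clock by equipment events. The C-arm acquires the IOCT scans, so docking precedes the first of them and parking follows the last. The IOCT window is therefore the scan-to-scan window plus two handling intervals. In POCT, nothing comparable before the first scan or after the last scan is counted.

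Randomization balances patients. It does not remove an offset written into the measurement rule of one arm. If the two techniques took equally long from first to last scan, the recorded means would still differ by the average handling time. If IOCT were faster on that scale, the same handling time would hide some or all of the advantage. This affects the one comparison for which the trial is sized.

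**Working it through.** **1. The two windows side by side**

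| | POCT | IOCT |
|---|---|---|
| Clock starts | first CT imaging begins | C-arm docks |
| First scan | same event as the start | planning scan, after docking |
| Last scan | same event as the stop | confirmatory CBCT, before parking |
| Clock stops | last CT scan ends | C-arm reaches park position |

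Matching scan anchors exist in both arms. They are used in POCT only.

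**2. The plan's own figures**

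Inputs from Sample size calculation and Data analysis: 24 per arm, alpha 0.05 two-sided, power 80%, 1:1 allocation, 10% dropout.

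- Dropout step: 24 / (1 − 0.10) = 26.7, rounded up to 27. This reproduces.
- The 24 cannot be reproduced, because the article gives no mean difference and no SD. Solving backwards with the normal approximation gives d = (1.960 + 0.842) × √(2/24) = 0.81 SD. With the noncentral t it is 0.826 SD. The design therefore aims at a difference of about 0.81 to 0.83 SD.

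**3. Effect of an offset**

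Let k be the mean docking-plus-parking time divided by the SD. Assume that it adds a constant to the IOCT times and leaves the SD unchanged. If the scan-to-scan means are equal, the t statistic is noncentral with 46 degrees of freedom and noncentrality k × √(24/2) = 3.464k. The test rejects when |t| > 2.013.

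The documents do not give k. The ranges below are assumptions: SD 8 to 15 min, handling time 2 to 5 min.

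- Smallest: 2/15 = 0.13 SD
- Middle example: 4/10 = 0.40 SD
- Largest: 5/8 = 0.625 SD

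| Offset k (SD) | Rejection rate, equal scan-to-scan times |
|---|---|
| 0 | 5.0% |
| 0.13 (2/15) | 7.4% |
| 0.20 | 10.4% |
| 0.30 | 17.4% |
| 0.40 | 27.4% |
| 0.50 | 39.6% |
| 0.625 | 56.3% |

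**4. Masking and exaggeration**

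If IOCT were truly faster by 0.826 SD from scan to scan, the measured advantage is 0.826 − k. Power falls from 80% to 56.5% at k = 0.2 and to 19.8% at k = 0.5. If IOCT were truly slower by 0.826 SD, the measured difference is 0.826 + k, and the rejection rate rises to 93.6% and 99.4%.

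**The case against.** The best defence is that docking and parking are part of localizing a nodule in a hybrid operating room, so counting them is a pragmatic measure of the time the method takes. That would be a coherent outcome if POCT also counted its own set-up and clearing, and it does not. The present mix measures neither imaging-to-imaging time nor total procedural burden.

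Several stronger readings are tempting, and the documents do not support them.

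- **The bias always runs against IOCT.** This holds only relative to scan-to-scan time. The IOCT-guided localization section puts anesthesia induction and lateral positioning before the first scan, and the IOCT clock starts only at docking. In POCT, draping, local anesthetic and the skin incision may fall inside the window, but their order relative to the first scan is not explicit. For total preparation effort the net direction is not established, and a scan-to-scan clock would not equalize every such step.
- **Any crossover patient has no valid time.** This applies only to a patient assigned to IOCT but localized by POCT, for whom no docking or parking occurs. A patient going the other way has both scans that the POCT clock needs. The text can also be read as following the procedure performed, and the handling of crossovers may be left to an analysis plan that is not shown.
- **The blinded assessor must know the arm.** The Randomization section says that "all of the study outcomes will be investigated by an independent assessor (blinded to the allocation of patients to either POCT or IOCT"). An arm-specific formula sits awkwardly with this, but the article does not say that the assessor, rather than the staff who manage the case record forms, calculates the duration. The point is secondary.
- **The false-positive rate is 7% to 56%.** These figures rest on assumed inputs, and the upper end pairs the smallest SD with the largest handling time. They are also not type I error rates for the outcome as the protocol defines it. They describe how often that outcome would differ significantly when scan-to-scan times do not.

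**Conclusion.** The point holds in this form: the sole primary outcome uses non-equivalent start and stop events, which lengthens IOCT relative to a common scan-to-scan clock, and the article neither justifies nor corrects this. That conclusion follows from the definitions alone and needs no assumed figure.

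The size cannot be determined from the documents. It could be close to negligible or large enough to decide the primary result, depending on handling time relative to the SD. A significant difference, or the absence of one, under the current definition could therefore not be attributed to the localization technique without a matching comparison.

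**What to change.** **Preferred, before analysis:** define one clock for both arms, from the start of the first planning scan to the end of the last confirmatory scan. Apply it to the procedure actually performed, which also gives IOCT-assigned patients localized by POCT a defined time. Report docking-to-park time separately, for example beside global operating room utilization time, which is already a secondary endpoint.

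**If scan times cannot be recovered for patients already treated, or the primary definition cannot be amended during recruitment:** keep the current definition, add the scan-to-scan comparison as a prespecified key sensitivity analysis, and do not attribute a difference to the technique unless both agree.

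**Cost:** no additional patients or procedures. It is nevertheless an amendment to the primary outcome of an open-label trial that has been recruiting since October 2018, so it needs to be dated and documented. The article does not say that scan time stamps are kept, so their availability must be checked first. Docking effort leaves the primary outcome. The retrospective study behind the sample size may have used the current definition, in which case the sizing basis should be checked against the common clock.
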